**Fig. 1 Fig1:**
[figure not shown]
The CARMS Trial design

### Study design: the qualitative component

There are four qualitative work-streams. The aim of the first is to investigate perceptions of both participants and health professionals, including mental health professionals, concerning aspects of the implementation of a psychological talking therapy focused on ameliorating suicidal thoughts and behaviours in people experiencing non-affective psychosis. The second work-stream explores psychological mechanisms which are perceived to be precursors and drivers to suicidal thoughts and acts. The third, examines acceptability of the experience of the therapy from the perspective of those randomised to CBSPp. The fourth work-stream investigates the experiences of participants taking part in research which has a suicide focus.

A purposive sampling matrix will be used to maximise diversity in the participants recruited to the qualitative work streams. Semi-structured, one-to-one, interviews will be used across all the qualitative work streams to generate the data.

### Recruitment to the RCT (the host site is Greater Manchester Mental Health NHS Foundation Trust)

Potential participants will be identified by mental health professionals in the participant’s mental health care team (including community mental health teams, early intervention services, and inpatient psychiatric wards) using the inclusion and exclusion criteria listed below. These professionals will then ascertain whether participants are willing to receive information about the study and to be contacted by a CARMS researcher. If so, potential participants will be contacted in order to provide them with a Participant Information Sheet (PIS) and to check eligibility for the trial. At least 24 h after receiving the PIS, participants will be asked to confirm whether they want to take part in the CARMS project and, if so, to provide informed consent.

Posters and flyers will be distributed in areas accessible to potential participants e.g., health service waiting rooms, inpatient wards, relevant community venues, where feasible. In addition, information about the CARMS trial will be disseminated via mental health charities. Recruitment materials will be used to enable participants to request that a member of their mental health care team (e.g., care co-ordinator) refer them into the CARMS trial. A dedicated CARMS website will also be used to provide information about the CARMS trial (https://sites.manchester.ac.uk/carms/). In addition, recruitment materials (e.g., posters, flyers, newsletters) will be distributed to mental health service providers. Members of the CARMS team, including researchers and therapists, will deliver mental health team briefings about CARMS as appropriate.

### Study design: eligibility criteria

The eligibility criteria are i. ICD-10 diagnosis relating to non-affective psychosis (ICD 10, i.e., F20 – F29), ii. self- reported experiences of suicidal thoughts, urges, plans and/or acts in the past 3 months, iii. in contact with mental health services and under the care of a mental health services clinical team (e.g., NHS community or inpatient mental health care teams, early intervention teams, crisis teams, home treatment teams), iv. aged 18 or over, v. sufficient English to complete questionnaires (hence, not needing an interpreter), vi. able to give informed consent as assessed by either a responsible clinician or by CARMS research staff following the British Psychological Society’s guidelines on gaining informed consent (http://www.bps.org.uk/sites/default/files/documents/code_of_human_research_ethics.pdf).

The exclusion criteria are i. dementia, or an organic brain disorder, ii. unable to complete assessments due to language barriers, and iii. currently taking part in a clinical trial. A short screening procedure will be used to assess eligibility.

### Study design: withdrawal criteria

The withdrawal criteria are i. the participant decides to withdraw from the trial for any or no reason, and ii. the participant is lost to follow-up. However, data will be included in the analyses up to the point of withdrawal with appropriate consent.

### Study design: randomisation and blinding

Randomisation will take place only when participants have consented to participate and after the baseline assessments have been completed. Hence, participants will consent to take part without knowing their group allocation. The Manchester Academic Health Sciences Centre (MAHSC), Clinical Trials Unit (CTU) will oversee the blocked stratified randomisation procedures. Researchers conducting the assessments, the trial statistician, one of the CARMS Trial Co-Principal Investigators, and members of the CTU conducting data handling and data monitoring will be blind to the randomised allocation group of participants. Procedures will be in place if a CARMS researcher becomes unblinded. In such an instance of unblinding then a different researcher will be allocated to work with that participant. We will not disclose the reason for this allocation. Indeed, we will strategically re-allocate researcher resource so that re-allocation is a frequent occurrence for researchers, especially given the wide geographical distribution of sites.

### Study design: sample size and power calculations

Based on power analyses, the target sample size is 125 participants in each arm (treatment and control), meaning that there will be a target of 250 participants in total for the primary analyses at 6 months across the participating sites. To account for attrition of 25%, it is anticipated that up to 333 participants will be recruited into the baseline phase of the trial. It is estimated that 50% of people approached will decline to take part. Therefore, approximately 666 participants will be identified as eligible and screened.

We will use an approach based on a simple t-test for the between group comparison in the primary suicide outcome measure which is specifically designed to account for differential clustering or partial nesting between the two arms [49]. It is implemented using the command clsampsi- in Stata [50]. This approach requires the following assumptions:
Effect size: A clinically meaningful difference on the primary suicide outcome variable (ASIQ) from baseline to the 6 month follow-up time-point is estimated as a 16 point reduction, which corresponds to an effect size of 0.42, based on pilot data [30].Attrition: We are allowing for an attrition rate of 25% from baseline to final follow-up.Clustering: we account for clustering of outcomes within the participants sharing a therapist in the treatment arm with an ICC = 0.02.Random allocation: 1:1 random allocation, 0.05 significance level, and 80% statistical power.

For our proposed mediational analyses to test psychological mechanisms, a sample size of approximately 250 has greater than 80% power to detect a proportion mediated of 35%, and over 70% power to detect a proportion mediated of 30% (calculated using PowerMediation in R).

In sum, our sample size will have sufficient power for our proposed efficacy and mediation analyses.

### Study design: study arms of treatment and control groups

#### Treatment arm: the CBSPp intervention plus TAU anticipated as 24 weekly 50 min sessions

The CBSPp intervention is a one-to-one, formulation based approach. Initial sessions focus on engaging the individual in exploring their suicidal thinking and behaviours and how they relate to key underlying psychological constructs and to their key emotions, cognitions and behaviours. Ways in which these types of thoughts and behaviours interact with their experiences of psychosis, life circumstances and history is also explored to reach a shared formulation and understanding of their suicidal thoughts, plans, and acts. The approach, collaboratively, generates possible actions which are likely to modify negative appraisals of emotional regulation, improve perceptions of social support, and perceptions of interpersonal problem solving, and to influence other main drivers of their suicidal thoughts and acts, for example, distressing symptoms of psychosis. As a consequence, it is hypothesised that perceptions of defeat, entrapment, and hopelessness will be improved indirectly, although, perceptions of defeat, entrapment and hopelessness will also be worked on directly during the therapy [14, 30, 31]. Therapists will be trained in CBT techniques and further trained in CBSPp.

#### Control arm: TAU only

TAU will include usual clinical care. This is likely to be, although not exclusively, in the form of assessment and intervention from a multi-disciplinary mental health team as an outpatient or inpatient, prescription of psychiatric medication, regular monitoring, and social support. Where possible, we will document the types of TAU offered to and/or received by participants.

#### Proposed outcome measures: primary, secondary, mechanistic, clinical, therapy process, and health economics variables

##### Primary suicide outcome measure

This is the *Adult Suicidal Ideation Questionnaire* [ASIQ] [51] which is a self-report measure comprising 25 items. Suicide ideation is a predictor of suicide attempts and suicide death [52]. Participants are asked to report the frequency of thoughts about death and suicide in the last month using a 7 point Likert scale. For individuals attending psychiatric outpatient clinics with a history of suicide attempts, internal consistency was reported as .97. Test-retest reliability was also reported to be high (r = .95) in a mixed sample including those with a history of suicide attempts [51]. The primary analyses examine changes in the ASIQ from baseline to the 6 month time-point.

##### Secondary suicide outcome measures

We will use the following measures, the first two of which are self-report measures.
*The Suicide Probability Scale* [53] comprises 36 items and measures four components of suicidal experiences including suicidal ideation, hopelessness, negative self-evaluations and hostility. The internal reliability for this measure was found to be high in a sample including psychiatric inpatients with a Cronbach’s alpha score reported as .93 [53].The *Beck Scale for Suicidal ideation* [54] measures recent suicidal ideation, plans, and intent over the past week (19 items) together with previous attempt history (2 items). This self-report measure has been reported as having an alpha coefficient of 0.96 and test–retest reliability of r = 0.88 with people who were psychiatric inpatients and with those with experiences of non-affective psychosis [55].*Self-reported frequency of suicidal thoughts, plans and attempts over the past 6 months.* Where feasible, we will collect data from clinical case notes and documentation of adverse events, including those considered to be serious.

##### Mechanistic outcome variables

Each mechanistic variable assesses key components of the predicted psychological pathways to suicidal experiences [22] using self-report questionnaires:
The *Difficulties in Emotional Regulation Scale* [56] measures self-reported appraisals of emotional control. Four aspects of emotional regulation comprise the scale which are i. an awareness and reflective capacity, or understanding, with respect to emotions, ii. the ability to accept thoughts and behaviours reflective of emotions, iii. feeling in control of emotional reactions, and iv. feeling able to use effective emotional regulation strategies. Typically, total scores on this scale have been found to correlate positively with a range of measures of psychological mental health problems in a large sample presenting at an outpatient psychiatric clinic. In addition, internal reliability was reported as 0.97 in this sample [57].The *Social Problem-Solving Inventory Short Form* [58] tests appraisals of social problem solving and has five sub-scales (positive problem orientation, negative problem orientation, rational, impulsive, and avoidant problem solving styles). Overall, there are 25 items. Alpha reliabilities have been reported as ranging between 0.85 and 0.96 in adolescents, young adults, middle aged and elderly adults [58].The *Social Support Appraisals Scale* [59] assesses perceptions of available social support using 23 items. Data generated from five heterogeneous student/college samples and five community samples indicated Cronbach’s alpha reliability calculations to be between 0.80 and 0.90 [59].The *Beck Hopelessness Scale* [60] measures perceptions of having a negative future with 20, binary choice, yes/no responses. Hopelessness has been shown to be a robust predictor of suicidal experiences even compared with measures of depressed mood states [61]. Reliability estimates have been recorded as exceeding 0.88 in a range of samples including those with suicidal thoughts and behaviours and severe mental health problems [60, 62, 63].The *Defeat and Entrapment scales* [64] assess perceptions of being defeated and trapped both of which use 16 items. Perceptions of both defeat and entrapment have been robustly implicated in pathways to suicidal experiences in people experiencing depression, anxiety [32], and also in those with non-affective psychosis [28]. In people with non-affective psychosis who also experienced some level of suicidal thoughts and behaviours, in the past or currently, the Cronbach’s alpha coefficients were reported to be 0.86 for defeat and 0.95 for entrapment [28].

##### Clinical variables

Mental health problems pertaining to psychosis, depression, and functioning, are measured in clinical interviews as follows: *Positive and Negative Syndrome Scale [PANSS]* [65], the *Psychotic Symptom Rating Scales [PSYRATS]* [66], the *Personal and Social Performance Scale [PSP]* [67] *and the Calgary Depression Scale [CDS]* [68]. The PANSS is the most widely used measure of positive, negative and general symptoms experienced by people with psychosis and was shown to have sound psychometric properties using a response analysis [69]. The PSYRATS shows excellent reliability across raters and has robust validity [66]. The PSP has excellent face validity and reliability with the majority of ratings taking place in those with schizophrenia [67]. The CDS was specifically designed for people with schizophrenia and was reported as having excellent reliability estimates [68].

Information about current medication for mental health problems (e.g., anti-psychotic and anti-depressant medication) will be recorded from self-reports and supplemented from clinical records where possible.

##### Health economics measures

Participant-level costs will be generated for each participant in both the CBSPp treatment and TAU control arms. Costs will comprise the costs of the intervention, of TAU, and downstream costs. Costs will be constructed from a combination of trial-based resource use (NHS contacts and the Client Service Use Receipt Inventory [CSRI] amended for our trial, to monitor service use) with published unit costs, allowing comparison of CBSPp with TAU in terms of costs to the NHS and PSS. Several methods are available to collect resource-use. The most popular have been resource-use questionnaires, resource-use diaries, and electronic record searches [70–72]. The Clients Service Receipt Inventory (CSRI) [73] is a commonly used method for the retrospective collection of resource-use information which has been implemented in the economic evaluation of a variety of physical and mental health care interventions [74–77]. The CSRI covers a range of economic factors including participant’s use of health and social care services, accommodation and living situation, income, employment and benefits (the CSRI is available from the Database of Instruments for Resource-use Measurement [DIRUM] website: http://www.dirum.org/assets/downloads/634462388066137028-CSRI.pdf). Similarly to other studies, we are using a modified version of the CSRI, based on the format and questions of the CSRI but ‘modified’ to reflect the care pathways of our study participants. Examples include the use of mental health care services (community teams, crisis teams, inpatient psychiatric admission),

The EQ–5D-3 L can reflect different levels of psychosis symptomatology, be responsive to intervention effects [78–80], and correlates with the PANSS and Brief Psychiatric Rating Scale - Expanded (BPRS-E) [81]. However, the EQ-5D-3 L showed significant ceiling effects compared with PANSS and BPRS-E. The EQ-5D-5 L [82] is less prone to ceiling effects in a range of health problems [83–86] and the increased sensitivity of EQ-5D-5 L may also favour Quality-Adjusted Life-Years (QALY) gains even if the changes in utility are smaller [87]. Hence we will use will use the EQ-5D-5 L. QALYs will be calculated by attaching available utility weights to the health states generated from the EQ-5D-5 L, using area under the curve methods with an assumption of a linear change between time points, controlling for baseline.

##### Demographic information

We will collect demographic information at baseline and then check at follow-up whether factors such as relationship status, work status and education have changed at the two follow-up periods of 6 and 12 months. We will collect data concerning age, ethnicity, gender, type of work, length of time doing this work, and highest level of education.

##### Assessment of mood

A visual analogue scale (0–100) will be used to assess mood prior to all assessment sessions, and after those sessions where possible. This is to get a very quick rating of whether the sessions have negatively impacted mood and will be used to feed into assessments of suicide risk.

##### Therapy process measures of therapeutic alliance, engagement and adherence

For those in the therapy arm of the trial, the therapeutic alliance will be assessed twice, after approximately four sessions and towards the end of the therapy, with the *Working Alliance Inventory – short form* [88] completed by the therapist and the participant. Therapists will also record the following information for each participant in the therapy arm of the trial as appropriate and where possible: i. number of sessions attended and ii. duration of each session.

### Data analyses of the CARMS RCT

#### Analysis of the trial data to assess efficacy

A statistical analysis plan will be prepared before any analysis is undertaken, and agreed with the independent DMEC and TSC. Reporting will follow the CONSORT for Psychological and Social Interventions. All analyses and summary statistics will be conducted on the Intention-To-Treat (ITT) population which is defined as all participants randomised regardless of completion of therapy or withdrawal from the study. All analyses will be carried out at the end of the last follow-up assessments, and no interim analysis is planned.

Consideration will be given to potential biases arising from loss to follow-up.

Analyses will be conducted in Stata version 16 or later. Descriptive statistics within each randomised group will be presented for baseline values. These will include counts and percentages for binary and categorical variables, and means and standard deviations, or medians with lower and upper quartiles, for continuous variables, along with minimum and maximum values and counts of missing values. There will be no tests of statistical significance or confidence intervals for differences between randomised groups on any baseline variable.

Treatment effects on primary and secondary outcomes will be estimated using linear mixed models fitted to outcome variables at all time points. Fixed effects will be NHS site, anti-depressant use at baseline (yes/no), baseline assessment for the outcome under investigation, treatment, time and time*treatment interactions. Participant will be included as a random intercept to account for repeated measures. If the number of therapists is different from the number of NHS sites, we will include therapist as an additional random effect.

Marginal treatment effects will be estimated for primary outcome (ASIQ score at 6 months), and for primary and secondary outcomes at all other time points, and reported separately as adjusted mean differences in scores between the groups with 95% confidence intervals and 2-sided *p*-values. Cohen’s D effect sizes will be calculated as the adjusted mean difference of the outcome divided by the sample standard deviation of the outcome at baseline. These will be displayed in a forest plot showing the treatment effects on the primary and the secondary outcomes at 6 months.

We will allow for the presence of missing data under the assumption that the data are Missing At Random, conditional on the covariates in the model, and as a sensitivity analysis include other baseline measures as predictors of future loss to follow-up.

To account for the possible prognostic effect of anti-depressant medication on outcomes, we will include anti-depressant use at baseline (yes/no) as a stratifying factor. We acknowledge that use of anti-depressant medication after randomisation might account for a proportion of any observed treatment effect because it might lie on the causal pathway between randomisation and outcome but it is not targeted by the intervention itself. If there is a significant differential effect in the uptake of anti-depressant medication between the treatment and control groups, we will assess the role of anti-depressant medication as a mediator, in addition to our hypothesised target mediators.

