### Study design: the RCT

The CARMS trial involves both an RCT and a nested qualitative component within the design. The trial was registered with ClinicalTrials.gov (reference NCT03114917) where it was first posted 14th April 2017. It was also registered with ISRCTN (reference ISRCTN17776666 10.1186/ISRCTN17776666) with registration being assigned 5th June 2017). Registration was accepted before recruitment commenced. The design of the trial follows Consolidated Standards of Reporting Trials (CONSORT; http://www.equator-network.org/reporting-guidelines/consort/) and SPIRIT guidelines (Standard Protocol Items: Recommendations for Intervention Trials; http://www.spirit-statement.org/), and the TIDieR checklist and guide; Template for Intervention Description and Replication (*BMJ* 2014; 348:g1687).

The design is a single-blind RCT with two parallel arms. Outcome variables assessing suicidal experiences will be collected at baseline, and at 6 and 12 months follow-up time points. Data pertaining to clinical and mediational variables will be collected at baseline, after therapy cessation (6 months), and at the 12 month follow-up time point. Health economics measures (assessed over the previous 6 months) will be collected at baseline and at the 12 month follow-up time-point to allow comparison over the pre-trial and post randomization period. It is anticipated that up to 24 individual therapy sessions, of up to an hour, will be offered over 6 months. Participants will be independently randomised to one of the two trial arms, with stratification based on whether the participant is or is not prescribed anti-depressant medication (as this could affect the primary outcome variable) and the NHS sites over which the trial is being tested (see Fig. 1).

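### The participant random intercept, in its usual form, assumes equal variance at 6 and 12 months, so the standard error of the 6-month primary contrast is mis-stated if the variances differ

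*Protocol article*

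**What the plan says.** The section Analysis of the trial data to assess efficacy specifies "linear mixed models fitted to outcome variables at all time points". The fixed effects are NHS site, baseline antidepressant use and "baseline assessment for the outcome under investigation, treatment, time and time*treatment interactions". On the repeated measures it says: "Participant will be included as a random intercept to account for repeated measures". One further random effect is conditional: "If the number of therapists is different from the number of NHS sites, we will include therapist as an additional random effect".

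The schedule is given under Study design: the RCT: "Outcome variables assessing suicidal experiences will be collected at baseline, and at 6 and 12 months follow-up time points". Baseline enters as a covariate, so two outcome visits remain, 6 and 12 months. The primary result is a contrast at one of them: "Marginal treatment effects will be estimated for primary outcome (ASIQ score at 6 months", reported "with 95% confidence intervals and 2-sided" p-values.

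The article does not describe the residual structure or the standard-error estimator, and it gives no ASIQ variance at either follow-up visit. It says that a statistical analysis plan will be written before any analysis. That plan is not shown.

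**The concern.** In its ordinary form, a random intercept with one residual variance over two visits is compound symmetry: a common variance at both visits and one covariance. The conditional therapist effect does not let the variance differ by visit. The primary inference, however, concerns 6 months alone. If the conditional variances at 6 and 12 months differ, the model-based standard error at 6 months borrows from the wrong visit, and the confidence interval and p-value of the primary comparison are off. The direction depends on which visit is the more variable. The same model serves the secondary scales.

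The article offers no reason to expect equal variances. Six months is the end of therapy, and 12 months is follow-up after it. The plan also relies on a missing-at-random assumption, under which likelihood inference leans on the covariance model, so a restriction that is not needed is harder to defend.

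**Working it through.** **Inputs from the protocol.** Sample size section: "1:1 random allocation, 0.05 significance level, and 80% statistical power"; 125 per arm analysed at 6 months; 16 ASIQ points as an effect size of 0.42; therapy-arm ICC 0.02; 25% attrition; up to 333 recruited.

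**The plan's own figure.** The implied SD is 16/0.42 = 38.1. Without clustering, 89 per arm are needed for 80% power. With ICC 0.02, about 125 per arm is recovered if roughly 6 therapists are assumed (noncentral t: 123 per arm, power 0.807 at 125) or roughly 3 (normal approximation: 126 per arm, power 0.799 at 125). The article does not state the number of therapists. Recruitment is 250/0.75 = 333.3, as stated. So 80% power at 6 months is a fair starting point.

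**Closed form.** Take complete data at both visits and the same covariates. With a treatment-by-time term, the 6-month contrast is estimated from the 6-month means. Its true variance is proportional to v6, but the model estimates one common variance, (v6 + v12)/2. With r = SD6/SD12 (conditional SDs):

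- k = model SE / true SE = sqrt((r² + 1)/2) / r
- type I error = 2[1 − Φ(1.96k)]
- power, starting from 80% = 1 − Φ(1.96k − 2.80)

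Example, r = 0.8: k = sqrt(1.64/2)/0.8 = 0.9055/0.8 = 1.13, and 1.96k = 2.22. Type I error is 2.7% and power is Φ(0.58) = 72%.

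| SD6/SD12 (assumed) | k | Type I error | Power |
|---|---|---|---|
| 0.8 | 1.13 | 2.7% | 72% |
| 0.9 | 1.06 | 3.8% | 77% |
| 1.0 | 1.00 | 5.0% | 80% |
| 1.1 | 0.96 | 6.1% | not comparable |
| 1.2 | 0.92 | 7.1% | not comparable |

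In the last two rows the test exceeds its nominal level, so its power cannot be set against 80%.

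**Simulation check.** REML fits, 3,000 replicates per scenario, residual correlation 0.6, without site or therapist effects. Two settings: 250 complete, and 333 randomised with 20% missing at 6 months and 25% at 12 months. The 20% is an assumption, not a protocol figure. Type I error at 6 months (complete / with dropout):

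| SD12/SD6 (= 1/r) | Planned model | Closed form |
|---|---|---|
| 0.8 | 6.9% / 7.9% | 7.6% |
| 0.9 | 5.8% / 6.4% | 6.2% |
| 1.0 | 4.7% / 5.2% | 5.0% |
| 1.2 | 2.8% / 3.3% | 3.0% |

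An unstructured covariance with baseline-by-time gave 4.8% / 5.0% in every scenario.

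**Role of baseline.** Two cases separate the baseline slope from the variance.

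- Equal raw variances, baseline correlation 0.6 at 6 months and 0.4 at 12 months (assumed). The conditional SDs are sqrt(1 − 0.36) = 0.80 and sqrt(1 − 0.16) = 0.92. In simulation the 6-month SE is about 5-9% too large and type I error is 3.3-3.6%, so the test is conservative.
- Slopes 0.7 and 0.4 with equal conditional variances. Type I error is 4.9-5.5%, and the single slope costs about 2% in precision.

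**The case against.** The strongest objection is that the article leaves the matter open. A random intercept is compatible with visit-specific residual variances or robust standard errors. Neither is excluded, and such detail commonly sits in the analysis plan. This stands in part: the article does not rule out a better residual structure, so there is no contradiction. But it is not silent either. It names the device for repeated measures, and a plan that follows that sentence in the ordinary way inherits the restriction. A random-intercept model of this kind is also a conventional analysis, so the point is a refinement.

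It is equally fair that the size is assumed throughout, because no follow-up variance is given. That stands in full.

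Three stronger readings are tempting, and the document does not support them.

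- **Inflated type I error.** This needs a larger conditional variance at 6 months than at 12, and nothing in the article suggests it. The more natural assumption, a weaker link with baseline at 12 months, points the other way. The article does not state that assumption either.
- **More dropout at 12 months makes the visits differ.** The sample size section uses one 25% figure, both to reach 250 at 6 months and for attrition to final follow-up. Dropout also does not in itself change the residual variance.
- **The single baseline slope separately makes the standard error wrong.** The last check above shows that it does not. It matters through the conditional variances.

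**Conclusion.** The point holds as a conditional weakness in a stated model. With the usual homoscedastic residual, the 6-month standard error is right only if the conditional variances at 6 and 12 months are equal. The documents fix neither the direction nor the size of any error. It is zero at equality, about 4-6% of the standard error at a 10% SD difference, and 8-13% at 20%. If the difference comes from a weaker baseline link at 12 months, the consequence is a conservative primary test with some loss of power. It would be wrong to infer that the planned test is known to exceed 5%. The figures rest on assumed variance ratios and, for the closed form, on complete data. The therapist effect was left out of the simulations. The change is worth making because it costs almost nothing and gives essentially the same result as the planned model when the variances are equal.

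**What to change.** In the efficacy analysis section, or in the analysis plan before any analysis, replace the participant random intercept with an unstructured residual covariance over the 6- and 12-month visits (two variances and one covariance). At the least, allow the residual variance to differ by visit. Optionally add a baseline-by-time term, so that the 6-month contrast uses its own baseline slope. Keep the other fixed effects and the conditional therapist term.

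Possible wording: *The residuals at 6 and 12 months will have an unstructured covariance within participant, and the baseline value of the outcome will interact with time.*

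The cost is one sentence, a standard option in the mixed-model command, and two parameters: one variance and one slope. With about 250 analysed this is negligible. Settling it in advance also avoids choosing the covariance after seeing the data.
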